**Methods:**

The objective of this multicentre, randomized, non-inferiority, controlled trial is to investigate whether 5 days of high-dose amoxicillin is associated with lower rates of clinical cure 14–21 days later as compared to 10 days of high-dose amoxicillin, the reference standard. Recruitment and enrolment will occur in the emergency departments of McMaster Children’s Hospital and the Children’s Hospital of Eastern Ontario. All children in the study will receive 5 days of amoxicillin after which point they will receive either 5 days of a different formulation of amoxicillin or a placebo. Assuming a clinical failure rate of 5% in the reference arm, a non-inferiority margin of 7.5%, one-sided alpha set at 0.025 and power of 0.80, 270 participants will be required. Participants from a previous feasibility study (n = 60) will be rolled over into the current study. We will be performing multiplex respiratory virus molecular testing, quantification of nasopharyngeal pneumococcal genomic loads, salivary inflammatory marker testing, and faecal microbiome profiling on participants.

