### Statistical analysis

#### Sample size

We estimate the baseline failure rate of standard therapy to be ~ 5%; this estimate is consistent with previous studies in children [13], is less than in similar adult studies [7], and is the approximate rate that was seen in the pilot study. We will use a non-inferiority margin of an additional 7.5%. As this is a non-inferiority trial, the crucial statistical comparison will be between the 97.5% (one-sided) CI of the difference between the failure rate of the experimental arm and the standard therapy arm; should the upper bound of this difference be smaller than 7.5%, a conclusion of non-inferiority will be reached. As the maximum baseline failure rate in the reference arm is probably 5%, the maximum failure rate in the experimental arm that would still be felt to be “non-inferior” would be 12.5%; the margin of 7.5% was selected to make the maximum failure rate in the experimental arm less than 13.5%, the median acceptable failure rate in the treatment of CAP identified in a survey of infectious-disease physicians [37]. Setting α at 5%, with 80% power, 135 participants in each arm will be required for this trial (PASS software package, NCSS LLC, Kayesville, UT, USA); as we will have accrued ~ 60 subjects in the pilot to be “rolled over”, an additional 210 participants will be required. Our experience conducting the pilot, combined with an analysis of visits to the EDs of the study sites, leads us to believe that this target should be achievable. It is estimated that the target sample size should be attainable after 2 years of enrolment.

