#### Analysis

We will use descriptive statistics to describe the baseline characteristics of the groups reported as count (percent) for categorical variables, and mean (standard deviation) or median (first quartile, third quartile) for continuous variables, depending on the distribution. We will adopt Consolidated Standards of Reporting Trials (CONSORT) criteria for reporting on non-inferiority and equivalence trials in reporting the trial [38]. The principal analysis will be per- protocol, as is recommended for non-inferiority trials [39–41]. The principal analysis is not intention-to-treat (ITT) simply because the effect of ITT analysis is to reduce the difference seen between treatment groups; in a superiority trial, ITT analysis functions to buttress a conclusion of superiority, but in a non-inferiority trial it could lead to a false conclusion of non-inferiority by masking a true difference between treatment arms.

We will use logistic regression to analyze binary outcomes, Poisson regression for count outcomes and linear regression for continuous outcomes. Descriptive analyses will be used to compare rates of viral and atypical co-infections in the entire study population and between groups.

We will perform some subgroup analyses by adding an interaction term between treatment group (5-day vs. 10-day course) and the following subgroups: (1) older (age 5–10 years) vs. younger (age <5 years); (2) higher vs. lower salivary CRP; and (3) virus/*Mycoplasma* detected in baseline NPS vs. no virus detected. These interaction tests will be exploratory in nature and not adjusted for multiple testing [42].

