These analyses will be exploratory. The following sensitivity analyses are planned: (1) intention-to-treat analysis; (2) strict per-protocol analysis including only those participants who were adherent to their medications and whose radiographs were reported by a radiologist to demonstrate alveolar infiltrates; (3) per-protocol analysis stratified by whether the saliva CRP was greater than the 75th percentile; and (4) per-protocol analysis stratified by whether a virus, an atypical pathogen, or high-level *S. pneumoniae* colonization was found in the NPS. If evidence is found of effect modification or confounding related to the above parameters additional analyses will be undertaken. The results of all analyses will be reported as estimate of effect, corresponding 95% CI and associated *p* values. All *p* values will be reported to three decimal places with those less than 0.001 reported as *p* < 0.001. The criterion for statistical significance will be set at alpha = 0.05. Table 1 provides a summary of the outcomes, corresponding hypotheses, measure, and method of analysis.

**Table 1 Tab1:** Variables, measures, and methods of analysis

Variable/outcome	Hypothesis	Outcome measure	Methods of analysis
Primary			
Clinical cure (per-protocol)	Short-course (5-day) treatment with high-dose amoxicillin is non-inferior to long-course (10-day) treatment	At visit (day 14–21) composite of: 1. Defervesced on or before day 4 2. No more than 1 further fever spike until visit 3. No tachypnoea and decreased work of breathing 4. No additional antibacterials given Dichotomous	Logistic regression
Secondary, between-group comparisons			
Absenteeism (caregiver, from work)	Short-course treatment is non-inferior to long-course treatment	Daily symptom diaries: self-reported number of caregiver-days absent from work (count)	Poisson regression
Absenteeism (child, from daycare/school)	Short-course treatment is non-inferior to long-course treatment	Daily symptom diaries: reported number of child-days absent from daycare/school (count)	Poisson regression
Mild drug adverse reactions	Fewer in short-course arm than in long-course arm	Daily symptom diaries: Reported number of child-days with diarrhoea, rash, abdominal pain, yeast infection (count)	Poisson regression
Anaphylaxis and other severe drug adverse reactions	Fewer in short-course arm than in long-course arm^a^	Daily symptom diaries, SAE reports. Dichotomous	Descriptive statistics

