Intention-to-treat	Results will remain robust	Clinical cure	Logistic regression
Strict per-protocol (those with adherence >80% and radiologist-verified pneumonia)	Results will remain robust	Clinical cure	Logistic regression

*SAE* serious adverse event, *RA* Research Assistant, *ARO* antibiotic-resistant organism, *CRP* C-reactive protein

^a^Too few events expected to be able to observe differences in treatment arms

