
The selection of the non-inferiority margin has a significant impact on trial outcome. It is clear that clinical considerations should inform the determination of the margin; if the margin is judged as unacceptably wide to clinicians, a “positive” non-inferiority trial will have little impact on practice. However, selection of the margin based solely on the clinical experience of the principal investigator should probably be avoided, despite how common this has been in the past. The US Food and Drug Administration (FDA) has provided guidance relating to statistical considerations affecting the selection of the non-inferiority margin [39]; note that their main concern seems to be that if the experimental treatment is found to be non-inferior to the standard therapy, there is sufficient evidence to be reasonably confident the experimental treatment is also superior to placebo [39]. The FDA draft guideline first instructs investigators to review meta-analyses of clinical trials of the standard therapy compared to placebo to discern the pooled estimate of efficacy; if only single trials are available, they can be used, but there will be much lower precision in the estimates of efficacy. Unfortunately, we cannot follow this guidance for the statistical determination of an appropriate margin for a trial such as SAFER because we do not have reliable data about the failure rate of placebo treatment of bacterial pneumonia in children living in the modern era. Estimates of child CAP-specific mortality from the pre-antibiotic era cannot be used since this would without doubt overestimate CAP-specific mortality in children today.

Adherence to medication is, in general, difficult to ensure. Caregivers of participants in this trial will be reminded far more frequently of the need to administer medication (via RA reminders and study diaries) than they would otherwise be; our adherence measures are similar to those in other major recent RCTs comparing short-course and standard-course antimicrobial therapy in children [56]. Despite this, it is entirely possible that adherence will be suboptimal, which could also predispose to a false conclusion of non-inferiority, especially if adherence to medication drops off after 5 days. From a practical standpoint, this is still important information for clinicians managing real patients, and would not greatly affect the generalizability of the results of the study (Additional file 1).

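### No planned analysis isolates adherence: the only adherence-restricted set also requires a radiologist-reported infiltrate, and its adherence rule treats the two arms differently

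*Protocol article*

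**What the plan says.** The Analysis section makes a per-protocol analysis principal. It puts ITT second because "in a non-inferiority trial it could lead to a false conclusion of non-inferiority by masking a true difference between treatment arms". The article does not list who is excluded from the principal per-protocol set.

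Adherence appears as an inclusion condition in one place, sensitivity analysis (2), the "strict per-protocol analysis including only those participants who were adherent to their medications and whose radiographs were reported by a radiologist" to show alveolar infiltrates. Table 1 repeats the pairing: "Strict per-protocol (those with adherence >80% and radiologist-verified pneumonia". The other sensitivity analyses are ITT and two stratified per-protocol analyses, by salivary CRP and by nasopharyngeal findings.

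Table 1 defines adherence, as a secondary outcome, as more than 80% of amoxicillin doses given. In the 5-day arm fewer than 3 of the first 15 doses may be missed; in the reference arm, fewer than 6.

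The Discussion says that poor adherence could lead to a false conclusion of non-inferiority, "especially if adherence to medication drops off after 5 days". It then accepts this as information of practical value to clinicians.

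**The concern.** A child randomised to 10 days who stops at day 5 has in effect received the experimental regimen. Such children pull the observed difference towards zero, which favours non-inferiority. The authors name this risk, so one would expect an analysis that shows how much it matters.

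The plan falls short in two ways.

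- **The restrictions are bundled.** Adherence and the radiologist's reading answer different questions. One concerns whether the assigned course was taken; the other concerns whether the child had the target disease, a separate dilution that the Discussion also raises. If the strict set gives a different answer, the plan cannot say which restriction caused it.
- **The adherence rule is asymmetric.** All children take a blinded product on days 6 to 10, so stopping at day 5 can occur in either arm. The Table 1 rule ignores the second product in the 5-day arm and counts it in the 10-day arm. The same behaviour therefore removes a child from one arm only.

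At stake is whether a non-inferiority result can be defended against the objection that many of the 10-day children took only 5 days.

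**Working it through.** **Inputs from the article.** Reference failure rate: "We estimate the baseline failure rate of standard therapy to be ~ 5"%. Margin: "We will use a non-inferiority margin of an additional 7.5"%. Abstract: "one-sided alpha set at 0.025 and power of 0.80, 270 participants will be required". Sample size section: "Setting α at 5%, with 80% power, 135 participants in each arm will be required for this trial". Decision rule: the upper bound of the one-sided 97.5% CI lies below 7.5%. Failure in the 5-day arm at the margin: 12.5%. Dosing is three times daily, so 15 doses in 5 days and 30 in 10.

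**Inputs assumed.** The share f of the 10-day arm that stops at day 5, and the failure risk of those children. The article gives neither.

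**1. The plan's own sample size.** Unpooled normal approximation, 5% failure in both arms, one-sided 0.025, 80% power:

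n = (1.960 + 0.842)² × 2 × 0.05 × 0.95 / 0.075² = 132.6, so 133 per arm.

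This agrees with the stated 135 to within 2 per arm. At 135 the power is 0.807 by the same formula. The sample size is not in question here.

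**2. The adherence rule applied to a day-5 stopper.**

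| Arm | Doses counted | Taken by a day-5 stopper | Missed | Allowed | Class |
|---|---|---|---|---|---|
| 5-day | 15 | 15 | 0 | fewer than 3 | adherent |
| 10-day | 30 | 15 | 15 | fewer than 6 | non-adherent |

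**3. Size of the dilution.** Set the true failure rates at 12.5% (5 days) and 5% (10 days). If stoppers take on the full 5-day risk, failure in the 10-day arm is 5% + 7.5% × f and the difference the trial sees is 7.5% × (1 − f). The table gives the exact binomial probability, at 135 per arm, that the upper bound falls below 7.5 points.

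| f | 10-day failure | Difference seen | Wald bound | Score bound |
|---|---|---|---|---|
| 0 | 5.00% | 7.50 | 3.3% | 2.2% |
| 10% | 5.75% | 6.75 | 5.0% | 3.6% |
| 20% | 6.50% | 6.00 | 7.3% | 5.6% |
| 30% | 7.25% | 5.25 | 10.3% | 8.2% |

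If stoppers take on only half the excess risk, 10-day failure is 5% + 3.75% × f, that is 5.375%, 5.75% and 6.125%. The Wald figures become 4.0%, 5.0% and 6.1%.

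The Wald rule exceeds its nominal 2.5% even without stoppers, so the dilution effect is the rise above 3.3%, not above 2.5%.

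**4. What the bundled set would leave.** With 80% adherent and 60% radiologist-positive (both assumed, independent), 135 × 0.8 × 0.6 = 65 per arm remain. Exact power at 5% failure in both arms is then 40% (score) to 55% (Wald). Adherence alone leaves 135 × 0.8 = 108 per arm, with power of 61% to 74%.

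**The case against.** **The principal set is not defined in the article.** A reader might infer that the deciding per-protocol analysis is known to keep day-5 stoppers. The article does not say so. Membership of the set may be fixed in the full protocol, and 'strict' could mean a tighter threshold added to a set that already drops gross deviators. This stands. It remains suggestive that adherence is introduced as a restriction of the strict set, and that the Discussion still treats poor adherence as a live threat, but that is inference.

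**The Discussion does not call this the main masking route.** It says that poor adherence could contribute, raises non-bacterial cases as well, and accepts the limitation for a pragmatic trial. This stands too. Disclosing the risk still does not measure it.

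**The combined set is a coherent stress test.** Removing two dilutions at once is reasonable, and a sensitivity analysis need not carry its own power. That justifies keeping it, but not having it as the only adherence analysis.

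**There are mitigations.** Adherence by arm will be reported, bottle volumes measured, and caregivers prompted by diary and two calls. Further analyses are promised if effect modification or confounding appears. These show how common non-adherence is; none commits to estimating the treatment effect without it.

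**The size is hypothetical.** It is. Stoppers may be children who are already well, and the half-risk figures are correspondingly smaller.

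**Conclusion.** The point holds in limited form. Two parts rest on the text alone: no listed analysis isolates adherence, and the Table 1 rule, if carried into the strict set, drops day-5 stoppers from the 10-day arm only. That one-sided exclusion removes children from one arm for behaviour that is kept in the other. If stopping is related to prognosis, it can bias the comparison in either direction.

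That the principal set has no adherence requirement is likely but not established. The figures in the working therefore describe what would follow if it has none: false non-inferiority of about 5% to 10% for 10% to 30% stopping at full 5-day risk, about 4% to 6% at half the excess risk, against 3.3% with no stopping (exact Wald). They rest on assumed stopping rates and on stopping otherwise unrelated to prognosis. They do not show that the trial's error rate is inflated, and the article does not support saying that it is.

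**What to change.** Replace sensitivity analysis (2), in the text and in Table 1, with three analyses:

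- **(2a) Adherence only.** Apply one rule to both arms that covers the blinded day 6–10 product as well as the first 5 days, so that stopping at day 5 has the same consequence in each arm.
- **(2b) Radiologist reading only.**
- **(2c) The present combined strict set.**

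Report 2a beside the principal and ITT analyses as supportive evidence. It should not be a condition for claiming non-inferiority. If 2a also had to pass the margin, simulated joint power (Wald, 5% failure in both arms) would be about 75%, 71% and 64% at 10%, 20% and 30% non-adherence, against about 81% for the principal analysis alone. The claim would also then hang on a subset chosen after randomisation.

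If the full protocol already sets an adherence threshold for the principal set, state it and reconcile it with the strict definition.

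The cost is revised wording and one or two extra model runs. Diaries, interviews, bottle volumes and the radiologist's reading are already being collected. The drawback is that 2a selects on post-randomisation behaviour, so it can be biased if stopping is related to how the child is doing.

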This definition of clinical cure is similar to that used in other studies of 5-day CAP therapy in children [13] and adults [7]. Our definition was created using explicit criteria to ensure transparency and maximize the generalizability of the results. However, to optimize the appropriateness of the definition, the criteria are somewhat complex; this is to ensure that “failure” in the trial would be associated with a clinical scenario that would merit a change in overall management, even if that change was as little as a requirement for additional follow up by the treating clinician. The first criterion of the definition states “significant improvement” in respiratory symptoms; this will be assumed to be present if the participant’s caregiver opines that the child has no functional limitation resulting from any residual dyspnoea/increased work of breathing. The second criterion notes that more than a single spike of fever is required for “failure” to avoid erroneous conclusions resulting from an errant thermometer reading. Fever of unknown aetiology will be presumed to be associated with bacterial respiratory illness, but participants with fever due to other discernible causes, whether viral (new respiratory illness documented by a nasopharyngeal specimen positive for a virus not present at the time of initial enrolment, clinical croup, stomatitis/herpangina, hand-foot-mouth disease, gastroenteritis with positive stool results, conjunctivitis, meningoencephalitis, viral hip synovitis, perimyocarditis or myocarditis, hepatitis) or bacterial (cellulitis and other soft tissue infections, septic arthritis/osteomyelitis, meningitis, urinary tract infection with positive urinalysis, or cholecystitis) would be considered to have met clinical cure criteria. Clearly, admission to hospital – even if antimicrobial treatment does not need to be changed – is not conducive to short-course therapy and merits a decision of treatment “failure”.

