#### Follow up

The RA will phone the caregiver once at day 3–5 and once at day 7–10 to verify the clinical stability of the participant. Caregivers will also be explicitly informed that they can contact the study team in the event of a concern prior to the scheduled phone calls. The caregiver will be given a study diary to complete each day, which will include the following: temperature, dyspnoea (older participants), increased work of breathing, school attendance, caregiver absenteeism from work duties, days of mild diarrhoea, mild (abdominal discomfort, rash) and severe (anaphylaxis) drug adverse reactions, and the number of missed medication doses, if applicable. The caregivers will be instructed how to take their child’s temperature and assess increased work of breathing. Any participant who has persistent fever more than 3 days post-enrolment will receive an additional 5 days of open-label amoxicillin after the initial 5 days (i.e. will receive a guaranteed 10 days of antimicrobial agents). Any participant who worsens clinically subsequent to enrolment at any time point prior to the primary outcome visit will be urged to seek medical care without delay either at the site where recruitment took place or with another physician (e.g. family physician, walk-in clinic); all participants will be provided with printed documentation about the SAFER trial and contact information for the local Principal Investigator (PI) for the benefit of the medical professional re-evaluating the participant. The criteria for permanent discontinuation of the experimental aspect of the study protocol in an individual subject are as follows: failure to defervesce by day 4 post-enrolment; requirement for hospitalization because of worsening respiratory illness; severe reaction potentially associated with amoxicillin, such as a generalized allergic reaction (urticarial rash, bronchospasm, angioedema, hypotension, etc.); requirement for prohibited concomitant medications; completion of treatment/intervention as defined by the protocol; or clinical reasons believed by the physician to be life-threatening.

The daily symptom diary will include prompts to aid caregivers to remember the three daily doses of study medication. The RAs will also encourage optimal adherence to medication administration at baseline and at each of the two scheduled follow-up phone communications.

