The participant will return to the hospital at day 14–21 for the measurement of the primary outcome and to deliver the study diaries. At this visit, the RA will verify whether the participant developed new fever or required additional antimicrobials, and will have a physician or nurse perform a brief physical examination (temperature, respiratory rate, and assessment of increased work of breathing). The medication bottles will be returned and the volume of remaining medication determined. The RA will phone the caregiver one month after enrolment to verify continued clinical stability. All attempts will be made to follow up participants, even those who are already known to represent clinical failure (e.g. do not defervesce by day 4 post-recruitment and receive 10 days of open-label amoxicillin) or who receive additional interventions outside of the study (e.g. have additional antimicrobial agents prescribed by other clinicians) to ensure completeness of data collection (Fig. 1).

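### The primary outcome is stated in two incompatible ways: Table 1 and Follow up make fever at day 4 a failure, the Primary outcome section does not

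*Protocol article*

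**What the plan says.** All places are in the protocol article.

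- **Study endpoints, Primary outcome.** Cure means meeting all of three criteria. The fever criterion allows at most one spike caused by bacterial respiratory illness from day 4 to the day 14–21 visit. The explanation adds that "more than a single spike of fever is required for" failure, that unexplained fever is presumed to be bacterial respiratory illness, and that "participants with fever due to other discernible causes", from a list of viral and bacterial conditions, "would be considered to have met clinical cure criteria". The third criterion covers additional antibacterials or admission because of lower respiratory illness. Defervescence by day 4 is not among the criteria.
- **Analysis, Table 1, primary row.** The composite begins "1. Defervesced on or before day 4 2. No more than 1 further fever spike until visit" and ends "4. No additional antibacterials given". Nothing exempts fever of another cause.
- **Follow up.** The treatment rule is "Any participant who has persistent fever more than 3 days post-enrolment will receive an additional 5 days of open-label amoxicillin". Permanent discontinuation of the experimental part of the protocol includes "failure to defervesce by day 4 post-enrolment". Children still to be followed include those "already known to represent clinical failure (e.g. do not defervesce by day 4 post-recruitment and receive 10 days of open-label amoxicillin").

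**The concern.** Table 1 does more than shorten the definition: it adds a component, and the Follow up section applies the same rule outside the table. Two assessors reading the same diary, one working from the Primary outcome section and one from Table 1, could code the same child differently.

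This outcome carries the non-inferiority test against a 7.5-point margin. About 7 failures are expected per arm (5% of 135 = 6.75), so the conclusion can rest on very few children. If the choice between the two rules is left until allocation is known, it will be open to challenge whichever way it is made.

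**Working it through.** **1. The two rules applied to the same child**

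| Child | Fever rule, Primary outcome section | Table 1 (and Follow up) | Status |
|---|---|---|---|
| Febrile on day 4 from a listed other cause | Met; the fever is excused | Item 1 fails | Clear conflict |
| One unexplained fever on day 4, gone by day 5 | Met; one spike only | Item 1 fails | Conflict, unless open-label amoxicillin counts as additional antibacterials, which is not stated |
| Fever resolving during day 4, then one later spike | Two spikes, or one if the child counts as afebrile by day 4 | Can be met | Ambiguous |
| Persistent unexplained fever from day 4 | Normally more than one spike: fails | Item 1 fails | Agree |

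**2. The plan's own sample size**

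Inputs (Abstract and Sample size): failure 5% in both arms, margin 7.5%, one-sided alpha 0.025, power 80%.

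n per arm = (1.960 + 0.842)² × 2 × 0.05 × 0.95 / 0.075² = 7.85 × 0.095 / 0.005625 ≈ 132.6, so 133. The stated 135 is reproduced within rounding and method.

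**3. How close one child is to the decision**

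Rule, with d = p1 − p0: non-inferior if d + 1.96 × √[p1(1−p1)/135 + p0(1−p0)/135] < 0.075. Take 7 control failures (7/135 = 0.0519).

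- 9 experimental failures (0.0667): 0.0148 + 1.96 × 0.0287 = 0.0711. Non-inferior.
- 10 experimental failures (0.0741): 0.0222 + 1.96 × 0.0295 = 0.0801. Not shown.

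**4. How often the definitions would disagree**

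The share of children affected is not in the document, so it is assumed: 0.1%, 0.5% or 1% of children fail only under Table 1. That is 0.135, 0.675 or 1.35 children per arm, with equal expectation in both arms. Power is the exact binomial probability of meeting the rule in step 3. Disagreement comes from 1,000,000 simulated trials with 5% failure under the Primary outcome section.

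| Share failing only Table 1 | Opposite conclusions | Power under Table 1, if the planned 5% belongs to the Primary outcome section | Power under the Primary outcome section, if the planned 5% belongs to Table 1 |
|---|---|---|---|
| 0.1% | about 2% | about 81% (failure 5.1%) | not tabulated |
| 0.5% | about 7% | about 78% (failure 5.5%) | about 85% (failure 4.5%) |
| 1% | about 11% | about 75% (failure 6.0%) | about 88% (failure 4.0%) |

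At exactly 5% failure the same rule gives 81.5%. If no child is affected, nothing changes.

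**The case against.** The strongest reply is that the Primary outcome section is the operative definition, that Table 1 is introduced as a summary, and that the typical day-4 failure is not in dispute. Much of this stands. A child with continuing unexplained fever fails both texts. Being a summary also explains why the table drops the admission item, the lower-respiratory indication and the 2-week limit. It does not explain an added component that Follow up repeats.

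The clear conflict is also narrow. A respiratory virus excuses fever only if it was not present at enrolment, and the Microbiology testing section describes nasopharyngeal testing of baseline specimens only. What mainly remains is a separate listed diagnosis, such as croup, stomatitis or urinary tract infection, that explains fever as early as day 4. This limits the numbers but does not remove the conflict.

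The full protocol or analysis plan might settle whether mandated open-label amoxicillin counts as additional antibacterials. That is fair for the second child in the table. It does not reach the first, where the article itself gives two answers.

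A reader might go further and infer three things that the document does not support:

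- **Bias towards one arm.** Both arms take the same amoxicillin for the first 5 days, so day-4 fever precedes any treatment difference.
- **A definite loss of power.** The direction depends on which definition the planned 5% belongs to, and the article does not say.
- **A proven contradiction for fever that resolves on day 4 and is followed by one spike.** This depends on whether defervescing on day 4 means that fever was still recorded that day.

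**Conclusion.** Wrong as written: the article gives two incompatible rules for the fever component of its primary outcome. The clear conflict is the child febrile on day 4 from an excused cause. The single unexplained day-4 fever is a second conflict unless open-label amoxicillin counts against cure.

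The effect is probably confined to a few children, but it falls on the deciding variable, where one child can matter near the margin. The disagreement rates of about 2%, 7% and 11% rest on assumed shares and on equal reclassification across arms; they illustrate sensitivity and do not estimate what will happen. It would be too strong to say that the failure count as a whole is undefined, since the two rules agree for most children.

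**What to change.** Before unblinding, choose one definition and align the Primary outcome section, the primary row of Table 1 and the example in Follow up to it.

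The simplest choice is to keep the Primary outcome section as the operative definition and add one sentence. It should state whether fever at day 4 that leads to the protocol-mandated open-label amoxicillin is a failure, and that the exemption for other documented causes applies to it. Which way the first part goes is the sponsor's decision. Table 1 items 1 and 2 should then be replaced by that fever criterion, and its remaining items matched to the section.

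The cost is mainly wording, with no new data collection. Recruitment has run since August 2016 and about 60 pilot participants are rolled over, so children already assessed may need recoding from existing diaries under the single definition.
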